Demographics and medical history	**x**															
Physical examination	**x**															**x**
Weight/height	**x**															
Urine pregnancy test^b^	**x**	**x**	**x**							**x**						
FSH test	**x**															
Urine drug screen	**x**	**x**	**x**							**x**						
Alcohol breath test	**x**	**x**	**x**							**x**						
Vital signs^c^	**x**		**x**							**x**						
12-lead ECG	**x**		**x**													**x**
Adverse events	**x**	**x**	**x**							**x**						
Concomitant medication	**x**	**x**	**x**							**x**						
Hematology, chemistry, coagulation^d^	**x**		**x**													**x**
COVID-19 test^e^	**x**	**x**	**x**							**x**						
Randomization		**x**														
Intake of amisulpride or placebo				**x**							**x**					
Breakfast^f^						**x**							**x**			
PK blood amisulpride^g^			**x**		**x**		**x**	**x**		**x**		**x**		**x**	**x**	
Headache severity NRS							**x**	**x**						**x**	**x**	
SCID-5-CV^h^	**x**															
MADRS^i^	**x**															
Columbia Suicide Severity Rating Scale^j^	**x**															
Questionnaires Psychopathology Set^k^				**x**	x	x					**x**	x	x			
MR Scanner trial activity Set 1^l^^((1), (2), (3), (4))^							**x**									
MR Scanner trial activity Set 2^l^^((1), (5), (6))^														**x**		
Behavioral paradigm^m^									**x**							

^a^There is a treatment-free interval of 7 ± 2 days between visits 3 and 4

^b^Urine pregnancy test (if urine test positive, blood test to be done)

^c^Vital signs: pulse rate, systolic and diastolic blood pressure (BP), and body temperature in the ear

^d^Hematology: leukocytes, granulocytes, neutrophils, eosinophils, basophiles, lymphocytes, monocytes, erythrocytes, thrombocytes, hematocrit, hemoglobin; chemistry: sodium, potassium, calcium, magnesium, total protein, albumin, glucose, creatinine, urea, bilirubin, ASAT, ALT, GGT, LDH, AP, CRP; Coagulation: aPTT, INR; * no coagulation at Visit 3 and 4

^e^Prior to Randomization

^f^Time window: 1:15 ± 15 min after amisulpride intake

^g^Time windows: 1:00 + 5 min, 3:30 + 30 min, 4:30 + 30 min

^h^SCID-5-CV (DSM-5, Beesdo-Baum, Zaudig, and Wittchen, 2019); * within 14 days prior to visit 3

^i^MADRS (Montgomery-Åsberg Depression Rating Scale, Montgomery and Åsberg, 1979); * within 14 days prior to visit 3

^g^Columbia Suicide Severity Rating Scale (C-SSRS, Posner et al., 2011); * within 14 days prior to visit 3

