^k^Questionnaires Set: Beck Depression Inventory (BDI; Beck et al., 1961); Snaith-Hamilton-Pleasure-Scale (SHAPS; Snaith et al., 1995); Dimensional Anhedonia Rating Scale (DARS; Rizvi et al., 2015); Leuven Affect and Pleasure Scale (LAPS; Demyttenaere et al., 2019)

^l^MRI: (1) high-resolution anatomical MRI scan; (2) resting-state functional magnetic resonance imaging (rsfMRI); (3) MID task; (4): instrumental learning fMRI task; (5) SID task; (6) effort-based decision-making fMRI task; (7) arterial spin labeling (ASL)

^m^Time window for probabilistic reward task: ± 30 min

Treatment with amisulpride or matching placebo occurs 3.5 to 4 h before the start of each scanning session. 1 to 1.5 h after the intake of amisulpride or matching placebo, subjects are served a standardized breakfast. Multimodal MR brain imaging (high-resolution anatomical MRI scan, resting state fMRI, task-based fMRI, arterial spin labeling (ASL)) is performed on two separate days where subjects first undergo an anatomical scan. On visit 3, the anatomical scan is followed by a resting state scan, two fMRI tasks (MID task [15] task and instrumental learning task (ILT) [21], an ASL sequence, and the probabilistic reward task (PRT) [18] as a pure behavioral measure of reward learning which is performed outside the scanner. The MID task is the first task presented inside the scanner to prevent it from being affected by fatigue as it is the primary outcome. On visit 4, the anatomical scan is followed by two different fMRI tasks (social incentive delay task (SID) [43] and effort-based decision-making (EBDM) task [20]. The SID task is presented before the EBDM task as physical effort is required to perform the assessments. Headache severity is measured using a numeric ranking scale to control for possible confounding of the MRI assessments by headache. MRI assessments are conducted at two visits to not exceed a scanning time of 60 min each. A timeline for substance administration and MR protocol for each experimental group at visit 3 and visit 4 can be found in Fig. 1. Time of treatment is standardized across subjects.

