### Relevant concomitant care

During the screening period, prior and concomitant medications are recorded and reviewed throughout the study until visit 4. In particular, prescribed medication or psychotherapy as mentioned above are not permitted as concomitant treatments. Subjects who have taken prescription or non-prescription medication may still be entered into the study, if, in the opinion of the investigator, the medication does not interfere with the study procedures or compromise safety. Amisulpride will not be used in combination with medications which, e.g., could induce torsade de pointes (such as class Ia and class III antiarrhythmic agents), as well as other medications as indicated in the label of amisulpride.

If concomitant drugs are administered, these are recorded in the subjects’ file and eCRF. Permitted concomitant treatments are not to be changed during the course of this study.

Moreover, the following criteria concerning diet and lifestyle result in the withdrawal of the study subject:Consumption of large amounts of caffeinated drinks (more than 8 cups of standard caffeinated drinks (tea, instant coffee) or 6 cups of stronger coffee or other drinks containing methylxanthines such as Coca-Cola or Red Bull per dayConsumption of caffeinated drinks 2 h prior to the start of the fMRI scanSmoking/nicotine consumption 2 h prior to the start of the fMRI scanConsumption of food containing poppy seeds within 24 h prior to visits 3 and 4Consumption of alcohol within 24 h prior to visits 3 and 4.

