### Group randomization

After written informed consent is obtained, healthy and MDD subjects meeting all in-/exclusion criteria are randomized at baseline (visit 2) or visit 3 to receive either amisulpride or matching placebo.

Treatments are randomly allocated in a 1:1 ratio. Randomization is performed in accordance with prepared randomization lists provided by an independent vendor of the Charité Research Organisation. A qualified external pharmacy performs a patient/subject individual re-packaging of the study medication in capsule boxes in accordance with the unblinded randomization list. Each capsule box is labeled with the respective randomization number and contains the study medication (amisulpride or matching placebo). The label does not allow any inferences about the administered compound.

The randomization list is kept in safe and confidential custody. Only personnel not involved in study conduction has access to the list. Additionally, sealed emergency envelopes containing information on the subject’s trial medication are provided to the Charité Research Organisation.

Thereupon, the unblinded Study Team of the Charité Research Organisation receives one capsule box with the corresponding tablet (amisulpride or matching placebo) for each patient/subject per visit. The blinded investigator administers two single doses of the same blinded study medication (amisulpride or matching placebo) to each subject according to the respective randomization number.

Additional randomization numbers are used in case of replacements being needed. The investigator enrolls study participants and documents the randomization number in the eCRF.

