### Sample size

Power analysis for a one-way ANOVA with 4 groups was conducted in G*Power [46] to determine a sufficient sample size using a one-sided alpha of 0.05, a power of 0.95, and a large effect size (*d* = 0.84). Previous studies in HV and in patients with MDD found large effects (*d* > 0.8), showing a significant increase in striatal activity after amisulpride administration as compared to placebo in patients with MDD [32, 35]. The sample size needed with this effect size is *N* = 102 completers. In order to have the same number of subjects per group, we aim for 104 completers, i.e., 26 per group. Accounting for a drop-out rate of ∼15%, the estimated total sample size is *N* = 120 (30 subjects per group).

Screening for the trial will stop once a sufficient number of subjects has been measured and controlled for dropouts due to excessive head movement in the scanner and/or headaches and incomplete data.

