### Protocol deviations and handling of missing values

Data from subjects who prematurely terminate the trial are used up to the maximum extent possible. Subjects who discontinue the trial early before the administration of study drug are replaced from the trial before the administration of the study drug. No procedures for replacing missing data are intended. All protocol non-compliances are listed and the reasons for exclusion of subjects from any of the analysis sets are listed. Where relevant, the data from these subjects is described separately.

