The clinical study protocol was first submitted on February 11, 2022, to the competent authorities. The independent ethics committee approved the protocol on March 3, 2022, with conditions. One condition was that it should be guaranteed that MDD patients enrolled in the trial were diagnosed and treated by staff experienced and certified for the treatment of major depressive disorder (psychiatrists, psychologists). The protocol amendment includes that subjects treated with antidepressants would not be included in the study and that subjects who received antidepressant treatment prior to study enrollment should not interrupt or wash out treatment for study purposes. Furthermore, it was specifically mentioned that no subjects with a QT prolongation at screening ECG should be enrolled in the study. An additional ECG assessment was included predose at Visit 4 for safety reasons. In addition, in the amended clinical study protocol clarifications to the study endpoints, study objectives, contraindicated concomitant medications, maximum number of subject replacements, treatment randomization, replacement in the event of headache, sample size, statistical analysis, and minor grammatical, formatting, or spelling corrections were made. After receiving final approval from the independent ethics committee and the Bundesinstitut für Arzneimittel und Medizinprodukte, recruitment was started.

Screening procedures of the first healthy volunteers revealed that the lower limits for systolic and diastolic blood pressure (100 mmHg and 65 mmHg) needed to fulfill eligibility criteria were defined too narrowly. More than 50% of all screened healthy volunteers could not pass the screening visit successfully. With an amendment of the clinical study protocol, the lower limits of blood pressure were reduced to 50 mmHg for diastolic blood pressure and to 90 mmHg for systolic blood pressure. Since a reflex tachycardia might occur in response to low blood pressure, the upper limit of the pulse rate was increased to 100 bpm (instead of 90 bpm) for inclusion. With the implementation of these new limits (after approval by the independent ethics committee and the Bundesinstitut für Arzneimittel und Medizinprodukte) the screening process was optimized resulting in a reduced screen failure rate.

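### Headache, rated only after dosing, is treated as a dropout reason and a confounder; removing, replacing or adjusting for it can bias the amisulpride–placebo contrast

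*Protocol article*

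**What the plan says.** Five places in the protocol article bear on who counts as usable and how headache is handled.

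- **Sample size.** The target is 104 completers out of 120. Screening ends when a sufficient number has been measured, "controlled for dropouts due to excessive head movement in the scanner and/or headaches and incomplete data". Headache stands beside unusable or missing data as a reason for loss.
- **Study design.** "Headache severity is measured using a numeric ranking scale to control for possible confounding of the MRI assessments by headache".
- **Table 1.** The row "Headache severity NRS" is marked at 3:30 and 4:30 h after dosing on both scan days. No predose rating is scheduled.
- **Protocol deviations and handling of missing values.** "Subjects who discontinue the trial early before the administration of study drug are replaced". Headache is not mentioned. Data from early terminators are to be used as far as possible, no imputation is intended, and exclusions are to be listed with reasons.
- **Discussion.** The amended protocol is said to clarify, among other items, "maximum number of subject replacements, treatment randomization, replacement in the event of headache, sample size, statistical analysis". The rule itself is not reproduced.

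Relevant concomitant care adds that "the following criteria concerning diet and lifestyle result in the withdrawal of the study subject"; the list includes caffeine or nicotine in the 2 h before the scan. The dose is given 3.5 to 4 h before the scan, so that window also lies after dosing.

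**The concern.** Randomisation makes the two arms comparable at the moment of dosing. A confounder of the drug–placebo contrast has to precede treatment. A headache rated 3.5 and 4.5 h after the tablet does not, and it may be a consequence of the drug.

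Two different operations follow from the text, and each can distort the primary comparison.

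- **Selection.** If subjects with headache are treated as dropouts or replaced, and the drug changes who has a headache, the remaining subjects in the two arms are selected differently. If headache is also related to the ventral striatum signal, the difference in means moves.
- **Adjustment.** If post-dose headache is entered as a covariate, any part of the drug effect that travels with headache is removed from the estimate.

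A subject with headache can still give a technically valid scan, so this goes beyond the unavoidable loss of images that cannot be analysed. Because no predose rating exists, no later analysis can substitute a baseline value.

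The replacement wording adds a practical problem. From this article a reader cannot tell whether a dosed subject with headache is analysed, excluded or replaced.

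**Working it through.** **1. The plan's own figure.** Inputs from Sample size: 4 groups, alpha 0.05, power 0.95, d = 0.84, hence f = d/2 = 0.42. The omnibus F test (df1 = 3, noncentral F with λ = N·f²) needs N = 102 (power 0.951); 104 gives 0.955. The stated figure reproduces. With 120 randomised and 104 completers, the plan allows for 120 − 104 = 16 losses, 16/120 = 13.3%.

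**2. Timing.**

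| Event | Time relative to dose | Source |
|---|---|---|
| Randomisation | before dose | Group randomization |
| Headache rating | +3:30 and +4:30 h only | Table 1 |
| Start of scan | +3.5 to +4 h | Study design |
| Caffeine/nicotine window | last 2 h before scan, so from about +1.5 to +2 h onward | Relevant concomitant care |

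The headache ratings and the lapse window both follow treatment.

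**3. Size of a selection effect (assumed inputs).** Suppose subjects are removed when a latent trigger exceeds a cut-off, and the trigger correlates r with BOLD. If a fraction p is removed, the mean BOLD of those who remain is r·m(p), with m(p) = −φ(z_p)/(1 − p).

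- m(0.05) = −0.1086
- m(0.15) = −0.2743
- m(0.20) = −0.3500

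Bias in the contrast = r·[m(p_amisulpride) − m(p_placebo)]:

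| Removed, amisulpride v placebo | r = 0.3 | r = 0.5 |
|---|---|---|
| 15% v 5% | 0.3 × (−0.1657) = −0.050 SD | 0.5 × (−0.1657) = −0.083 SD |
| 20% v 5% | 0.3 × (−0.2414) = −0.072 SD | 0.5 × (−0.2414) = −0.121 SD |
| 13.3% v 13.3% | 0 | 0 |

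As a share of d = 0.84: 0.050/0.84 = 6% and 0.121/0.84 = 14%. A simulation holding the average loss at 13.3% (20% v 6.7%) gave 0.042, 0.063 and 0.106 SD for r = 0.2, 0.3 and 0.5, which agrees. The sign reverses if r is negative.

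**4. Size of an adjustment effect (assumed inputs).** If the drug shifts headache by a SD and BOLD changes by b SD per SD of headache, adjustment moves the estimate by a·b: 0.3 × 0.3 = 0.09 SD, or 0.5 × 0.3 = 0.15 SD.

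**5. Consequence.** For one two-arm contrast with 26 per arm, SE = √(2/26) = 0.277 SD. A bias of 0.10 SD against the effect lowers power at d = 0.84 from 0.857 to 0.761 (two-sided 0.05, normal approximation). With no true effect it raises the type I error from 0.050 to 0.065.

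**6. Cost of keeping subjects.** Omnibus power at f = 0.42 is 0.955 with 104 analysable and 0.978 with 120. Retaining headache cases needs no larger sample.

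**The case against.** The best reply has four parts.

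- **No headache term is in the stated model.** Statistical analysis names treatment, group and their interaction only. The measuring purpose given in Study design could mean a check or a sensitivity analysis, and the detail is left to an analysis plan not shown. This stands: a reader might infer that the primary model adjusts for headache, but the article states an intention, not a model term.
- **The passages may not conflict.** The missing-values section says that subjects lost before dosing are replaced; it does not say that only they are. The sample-size sentence is a rule for stopping screening and defines no analysis set. The full protocol may hold a clear headache rule. This stands in part: there is no proven contradiction, but the passages differ and the article never joins them.
- **The magnitude is assumed throughout.** No arm-specific rate or correlation is given, and Pharmacological intervention describes low doses as well tolerated. Even 0.121 SD is under half a standard error (0.121/0.277 = 0.44). The hypothesis is an effect in MDD but not in HV, and drug-related selection acting alike in both groups would largely cancel in that interaction. All of this stands. It limits the size without removing the mechanism.
- **Blinding.** Investigators and analysts are blinded. That restrains discretionary exclusion, but not exclusion caused by the drug itself.

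Stronger readings are tempting, and the text does not carry them. A reader might say that randomisation is undone. Bias needs exclusion linked to both arm and BOLD, and the planned loss is about 13–15%. A reader might also object to randomising at visit 2, but blinded losses before dosing cannot depend on the drug. Removing scans for head movement is likewise no error in itself: some loss is unavoidable in fMRI, and the threshold may sit in the unseen plan. What matters there is that the limit is applied blind. Nor do the documents say that a scan already acquired is discarded after a caffeine or nicotine lapse; the missing-values section points the other way.

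**Conclusion.** The point holds for headache. The article counts headache as a reason for loss, refers to replacement because of it, and calls it a possible confounder, although it is rated only after randomised dosing. Acting on that in the primary analysis would select or adjust on a possible drug effect.

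The size cannot be determined from the document. The range of 0.05–0.12 SD rests on assumed removal of 15–20% v 5% and correlations of 0.3–0.5. It is zero when rates and mechanism match between arms. This is a moderate weakness worth correcting because the correction is cheap. It is not evidence that the trial's comparison is invalid.

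**What to change.** 1. Define the primary analysis as every randomised, dosed subject with a technically usable MID scan, in the arm assigned, regardless of headache. Apply the image-quality and motion limit blind to arm and group.
2. Where a scan exists despite a recorded caffeine or nicotine lapse, keep it in the primary analysis and flag the deviation. This concerns only the handling of data already collected; the withdrawal rule is not at issue here.
3. Use post-dose headache, whether as exclusion or covariate, only in a labelled sensitivity analysis.
4. Report headache ratings and scan exclusions, with reasons, by arm and diagnostic group. Subjects for whom no scan was acquired belong in that table too, since no analysis choice recovers them.
5. Reconcile Sample size, the missing-values section and the headache replacement mentioned in the Discussion so that they state one replacement rule.
6. Optionally, add one predose headache rating per scan day if a baseline adjustment is wanted. As recruitment is described as ongoing, this would help only subjects not yet scanned.

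The cost is wording, one table and, if chosen, a single-item rating. The downside is that some noisier scans stay in the primary analysis. No increase in sample size is needed.

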### Protocol deviations and handling of missing values

Data from subjects who prematurely terminate the trial are used up to the maximum extent possible. Subjects who discontinue the trial early before the administration of study drug are replaced from the trial before the administration of the study drug. No procedures for replacing missing data are intended. All protocol non-compliances are listed and the reasons for exclusion of subjects from any of the analysis sets are listed. Where relevant, the data from these subjects is described separately.

### Data management and monitoring

Data is entered by the data entry team of Charité Research Organisation into the eCRF medrio. Instructions for use of the system and completion of the eCRF is outlined in the eCRF completion guideline. Quality assurance reports are generated to ensure study data are clean, accurate, and complete. Quality assurance reports include, but are not limited to, the following: missing forms, missing and out-of-range values, automated data queries, and targeted manual reviews of study data. Charité Research Organisation monitoring staff conduct site visits for source data verification to ensure appropriate quality and completeness of data. Discrepancies in data entry in eCRFs will trigger data re-entry requirements and/or site retraining for the relevant data fields.

For each subject randomized, an eCRF is completed within the Electronic Data Capture (EDC) system and approved by the investigator.

All data entered in the eCRF is verifiable in source documentation other than the eCRF. Source documents are filed at the trial site according to local standard operating procedure (SOP). Trained study site staff is responsible for entering subject source data into the validated EDC system. Data captured electronically is immediately saved to the applicable database and changes are tracked to provide an audit trail. Data validation procedures are applied by Data Management to each stage of data handling to ensure that all data are reliable and have been processed correctly.

Data Management SOPs are in place for EDC Setup, EDC User Management, Data Validation, and Database Lock. The EDC database is locked once all expected data are captured in EDC, all discrepancies are resolved and all medical/surgical terms and medication are classified by the latest versions of Medical and Drug dictionaries.

The medical operations team and the project management team of the Charité Research Organisation organize and perform site training, monitoring, and close oversight of all study visits to ensure proper adherence to the clinical trial protocol and to international research standards. Monitoring visits include regular review of data submission forms, source data verification, informed consent documentation, and adverse event reporting. The sponsor (MSB Medical School Berlin) also monitors compliance with the protocol and Good Clinical Practice.

